## Abstract

**Introduction/aim:** The supraphysiologic chloride concentration of normal saline may contribute to acute kidney injury (AKI). Balanced crystalloids can decrease chloride concentration and AKI in critically ill patients. We aim to test the hypothesis that, in patients with predicted severe acute pancreatitis (pSAP), compared with saline, fluid therapy with balanced crystalloids will decrease plasma chloride concentration.

**Methods/Design:** This is a multicenter, stepped-wedge, cluster-randomized, controlled trial. All eligible patients presenting to the 11 participating sites across China during the study period will be recruited. All sites will use saline for the first month and sequentially change to balanced crystalloids at the pre-determined and randomly allocated time point. The primary endpoint is the plasma chloride concentration on day 3 of enrollment. Secondary endpoints will include major adverse kidney events on hospital discharge or day 30 (MAKE 30) and free and alive days to day 30 for intensive care admission, invasive ventilation, vasopressors, and renal replacement therapy. Additional endpoints include daily serum chloride and sequential organ failure assessment (SOFA) score over the first seven days of enrollment.

**Discussion:** This study will provide data to define the impact of normal saline vs. balanced crystalloids on plasma chloride concentration and clinical outcomes in pSAP patients. It will also provide the necessary data to power future large-scale randomized trials relating to fluid therapy.

**Ethics and Dissemination:** This study was approved by the ethics committee of Jinling Hospital, Nanjing University (2020NZKY-015-01) and all the participating sites. The results of this trial will be disseminated in peer-reviewed journals and at scientific conferences.

**Trial registration:** The trial has been registered at the Chinese Clinical Trials Registry (ChiCTR2100044432).

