## Introduction

The most important determinant of mortality in patients with acute pancreatitis (AP) is organ failure (1). Renal failure or acute kidney injury (AKI) occurs in 25–59% of patients with severe AP (2, 3). It may be due to several factors, including hypovolemia, hypoxemia, pancreatic proteolytic enzymes, impairment of renal microcirculation, decreased renal perfusion pressure, tissue edema, and/or intrabdominal hypertension (4–6). Maintaining normovolaemia by timely and adequate fluid therapy to preserve organ perfusion is considered the cornerstone of the management of AP in the acute phase (7–9).

Normal saline (NS or 0.9% sodium chloride) is the most frequently used isotonic crystalloid fluid for resuscitation in the acute setting around the world (10). Because the chloride concentration of NS (154 mmol per liter) is significantly higher than plasma chloride concentration (94–111 mmol per liter), there is a risk of hyperchloremic metabolic acidosis. The risk of this increases with systemic inflammation and impaired renal perfusion through multiple mechanisms (11). However, the clinical impact of the increased chloride load with NS resuscitation is not fully understood. There is some evidence that it increases the risk of AKI and the need for renal replacement therapy (RRT) in critically ill patients (12, 13), but there is no reliable data in AP patients.

Balanced crystalloid fluids are an alternative to NS, and some current guidelines recommend Lactated Ringers (LR) for early resuscitation, but there is a lack of high-quality evidence (7, 8, 14). Previous studies showed that LR resuscitation can decrease inflammatory markers but did not improve clinical outcomes in patients with predominantly mild AP (15–17). These studies did not report changes in plasma chloride or the incidence of AKI. Our previous study showed that aggressive resuscitation and increased chloride load during the first 24 hours were risk factors for new-onset AKI in patients with moderately severe and severe AP (18). This study aims to compare the impact of NS and a balanced crystalloid fluid on the plasma chloride concentration and the incidence of AKI in patients with predicted severe AP (pSAP).

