### Endpoints

#### Primary Endpoint

The primary endpoint is plasma chloride concentration on the morning of day 3. The day 3 chloride will be the chloride measured in the morning bloods on the third day after enrollment, with the day of enrollment labeled day 1, the next day labeled day 2, and the following day labeled day 3. Thus, the measurement of day3 chloride will typically be 36–48 h from enrollment. The time point is chosen because high-rate intravenous fluid administration is expected during this period (initial 24–48 h), as early aggressive hydration is recommended in AP patients (23).

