##### Part III: Biochemical Endpoints

Highest creatinine in the first seven days.Highest serum chloride in the first seven days of enrollment.Daily serum chloride from day1 to day 7.Daily serum bicarbonate from day1 to day 7.Plasma NGAL concentration at day1, day2, day3, and day5.Healthcare resource use (hospital expenditure) during the index admission.

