### Statistical Analysis

The reporting and presentation of this trial will follow the CONSORT guidelines for stepped-wedge trials (24). Based on the principle of intention to treat (ITT), a full-analysis set (FAS) will be performed on the population with outcome reporting (day3 chloride concentration). FAS will be used for the analysis of baseline characteristics and main therapeutic interventions. The safety set (SS) will include all enrolled patients for assessing the safety profile of the intervention.

Descriptive statistics will be used to assess any marked baseline differences in demographics or outcome measures between the two groups, taking clustering into account. Comparisons of binary outcomes will be expressed as relative risk with 95% confidence intervals and comparisons of continuous outcomes as mean differences together with 95% confidence intervals. Between-group comparisons will be made using generalized linear mixed-model (GLMMs) with a hospital-level random effect to address clustering by hospital and random slopes of time to account for temporal effects, as delineated by Hussey and Hughes. Two-sided 5% significance levels will be used to identify statistically significant results. All confidence intervals reported will be 95% confidence intervals.

A series of subgroup analyses will be conducted for the evaluation of the primary endpoint: age (dichotomized at 60 years old), referral or non-referral, presence of AKI at enrollment, and presence of organ failure at enrollment.

For any possible missing data, we assume the data is missing at random while performing analyses by GLMM. Moreover, a series of sensitivity analyses after imputing the missing primary outcome using worse-case (i.e., values at baseline), Last Observation Carried Forward (LOCF), and multiply imputation will be used to validate and test the robustness of our trial result.

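### The imputation labelled worse-case uses the baseline chloride, a no-change value given alike to both arms, so the planned sensitivity analyses do not bound missing-data departures unfavourable to balanced crystalloid

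*Protocol article*

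**What the plan says.** The Primary Endpoint section sets the outcome: "The primary endpoint is plasma chloride concentration on the morning of day 3". The hypothesis in the Abstract is that "fluid therapy with balanced crystalloids will decrease plasma chloride concentration" compared with saline, and the target difference in the sample-size section is 1.5 mmol/L with an SD of 6 mmol/L.

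On missing data, the Statistical Analysis section makes three statements:

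- The analysis set contains only patients who have the outcome: "a full-analysis set (FAS) will be performed on the population with outcome reporting (day3 chloride concentration").
- For the main model, "we assume the data is missing at random while performing analyses by GLMM".
- Sensitivity analyses follow after "imputing the missing primary outcome using worse-case (i.e., values at baseline), Last Observation Carried Forward (LOCF), and multiply imputation", and these "will be used to validate and test the robustness of our trial result".

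The biochemical endpoints include "Daily serum chloride from day1 to day 7", so a day-2 value is planned between baseline and the primary time point.

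**The concern.** A worst-case analysis should give missing patients values that count against the claim being tested. Here the claim is that chloride is lower on balanced crystalloid. The unfavourable values are therefore high chloride in the balanced arm and low chloride in the saline arm. Baseline is neither by construction: it is each patient's own starting value, assigned by the same rule in both arms.

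The Introduction gives the expected direction under saline: "Because the chloride concentration of NS (154 mmol per liter) is significantly higher than plasma chloride concentration (94–111 mmol per liter"). A baseline value for a saline patient is thus probably below the day-3 value it replaces. That pulls the comparison toward no difference, but not past it.

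The label matters because the analysis set leaves out patients without a day-3 value. The imputations are the only stated place where those patients enter the primary-endpoint analysis. A report could say that the result survived a worst case when no unfavourable case was examined.

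**Working it through.** The article gives no missing-data rate and no figure for these sensitivity analyses, so there is none to reproduce. The calculation below is an illustration.

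**Inputs from the article:** target difference 1.5 mmol/L, taken as D = −1.5 (balanced minus saline); SD 6 mmol/L; two-sided 5%; stated power 90%.

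**Assumptions:** missing share m of 5%, 10% or 20%, equal in both arms; balanced baselines; for LOCF, a day-2 difference half the day-3 difference.

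**Formulas**

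- Any imputation: estimate = (1 − m) × D + m × (difference among imputed values).
- Baseline value: the imputed difference is 0, so estimate = (1 − m) × D. At 10%: 0.90 × (−1.5) = −1.35.
- LOCF when every missing patient has a day-2 value: (1 − m) × D + m × D/2. At 10%: −1.35 − 0.075 = −1.425.
- LOCF when none has a day-2 value: the same as baseline imputation.
- Shift of delta in the balanced arm only: D + m × delta. At 10% with delta 6: −1.5 + 0.6 = −0.90.
- Opposite shifts in both arms: D + 2 × m × delta. At 10% with delta 6: −1.5 + 1.2 = −0.30.

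| Treatment of missing values | m = 5% | m = 10% | m = 20% |
|---|---|---|---|
| Missing at random (delta = 0) | −1.50 | −1.50 | −1.50 |
| Baseline value | −1.43 | −1.35 | −1.20 |
| LOCF, all have day 2 | −1.46 | −1.43 | −1.35 |
| LOCF, none has day 2 | −1.43 | −1.35 | −1.20 |
| +6 in balanced arm only | −1.20 | −0.90 | −0.30 |
| +6 balanced, −6 saline | −0.90 | −0.30 | +0.90 |

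**Shift that brings the estimate to zero:** in one arm 1.5/m = 30, 15 or 7.5 mmol/L; in both arms 1.5/(2m) = 15, 7.5 or 3.75 mmol/L per arm.

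**Shift that removes significance:** this is smaller. The stated 90% power implies a standard error of 1.5/(1.960 + 1.282) = 0.463, hence a significance bound of 1.960 × 0.463 = 0.907. An estimate of −1.5 can move by 0.593 before it crosses that bound. At 10% missing this takes 5.9 mmol/L in one arm, or 3.0 in each. At 5% it takes 11.9 or 5.9. These figures take the power statement at face value. A calculation from the article's own design inputs gives a standard error of 1.085, under which −1.5 would not be significant at all. That is a separate matter, and the point estimates in the table do not depend on it.

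**The case against.** The strongest reply is that baseline imputation is conservative for a superiority question. It assumes no treatment effect in the missing patients and pulls the estimate toward zero. That stands, given balanced baselines. It is a mild penalty of fixed form, though: it can never take the estimate past zero, and it is not an upper limit on harm to the conclusion.

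Three stronger readings are tempting, and the article does not support them.

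- **That baseline imputation and LOCF are often the same analysis.** Daily chloride is planned, so LOCF normally carries the day-2 value. The two coincide only for patients whose day-2 value is also missing, and how often that happens cannot be known from the article.
- **That the sensitivity analyses cannot test robustness.** Baseline imputation and LOCF do depart from missing at random, in a direction toward no difference. Multiple imputation brings back the excluded patients and may use day-1 and day-2 chloride, which could make its missing-at-random assumption weaker than that of the main model. The imputation model is not given, and that detail may sit in the analysis plan.
- **That day-3 values will be missing mainly through death, transfer or early discharge.** The article does not say so. It excludes patients expected to die within 24–48 hours and measures the endpoint typically 36–48 hours after enrollment, so losses may be few.

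It is also fair to say that the shifts needed to bring the estimate to zero are large when little is missing (30 mmol/L in one arm at 5%), and that a delta specification often belongs in the analysis plan. Its absence from the article is not the finding. The finding is that the article fixes the content of the worst case, and fixes it as something else.

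**Conclusion.** The point holds in a limited form. The rule is mislabelled, and none of the three stated methods shifts missing values against balanced crystalloid, so the set does not bound unfavourable departures from missing at random. At an assumed 5–10% missing, the so-called worst case moves a 1.5 mmol/L difference by 0.075 to 0.15. A one-SD unfavourable shift in one arm moves it by 0.3 to 0.6, four times as much.

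The size rests on the assumed missing rate, equal missingness in the arms and balanced baselines. If hardly any day-3 values are missing, the practical effect is small. The primary analysis itself is not affected; what is at risk is the claim of robustness attached to it.

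**What to change.** Rename the rule baseline-value imputation. Define the worst-case analysis as a delta-adjusted multiple imputation that is specific to arm:

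- Impute under missing at random, then add delta to imputed day-3 chloride in the balanced arm and subtract delta in the saline arm.
- Run delta from 0 to 6 mmol/L (one SD), and extend the range until the conclusion changes. The extension is needed because, at low missingness, 6 mmol/L may not reach that point.
- Report the tipping delta, with delta = 0 as the reference, next to the number and reasons of missing values by arm, so that readers can judge whether it is plausible.

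Baseline-value imputation and LOCF need not be dropped and can remain as secondary checks. The cost is one or two sentences in the analysis section and a little programming. No extra data are needed.

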### Adverse Events

All the participating sites and clinical teams will be required to report all adverse events to the CAPCTG coordinating center. An independent data safety and monitoring board (DSMB) (consisting of a surgeon, an intensivist, and a statistician) will oversee all aspects of patient safety. The DSMB will review all the safety profiles regularly (every 2 months) during the study period. Adverse events (AE) will be reported in a uniform format through the electronic data capture system.

## Discussion

The best crystalloid for the early resuscitation of patients with AP remains controversial. The CLEVER-AP trial will, for the first time, provide evidence regarding the effects of normal saline and balanced crystalloid fluid on plasma chloride concentration and AKI in patients with pSAP. The findings of this trial will have direct clinical consequences as it will provide definitive evidence.

MAKE30 is identified as a key clinical endpoint, and it has been used successfully in several fluid trials (12, 25). MAKE30 is the composite of death, new RRT, or persistent renal dysfunction (PRD), which is recommended by the National Institute of Diabetes and Digestive and Kidney Diseases (NIDDK) workgroup for capturing effects of the short-term or longer-term evolution of AKI (26, 27). As such, it is a patient-centered and highly relevant endpoint for clinical research. Adopting MAKE30 as a key secondary endpoint will allow comparison with other major trials conducted with different patient populations.

The stepped-wedge cluster randomized design is adopted for the CLEVER-AP trial based on both methodology and clinical merits it could provide. From the methodology perspective, it uses the hospital as the entity of randomization because this will minimize the risk of treatment contamination and could greatly reflect the real-life practice across each hospital compared to randomization at the patient or physician level. Moreover, this design could model and assess the underlying temporal trends of the intervention with all hospitals accessing the intervention at the end of the rollout period. From the clinical perspective, since massive intravenous fluid infusion is essential and crucial in managing early acute pancreatitis, randomization at the patient level would make the intervention (fluid infusion with different types of crystalloids) vulnerable to misuse, potentially leading to contamination (12, 28). Moreover, the routine consent-and-randomization process in patient-level randomized trials takes a lot of time, during which no one knows what fluid should be used before randomization. Therefore, intravenous fluid before randomization, which could be massive, could significantly confound the trial results.

The CLEVER-AP trial is sponsored by Jinling Hospital of Nanjing University, which is the national referral center for AP, admitting more than 800 cases of AP annually. The trial will be coordinated by the CAPCTG coordinating center (capctg.medbit.cn), which is capable of and experienced in conducting nationwide trials (29, 30).

In conclusion, the CLEVER-AP trial aims to evaluate the effects of balanced crystalloids vs. NS on plasma chloride concentration, major adverse kidney events, and clinical outcomes in predicted severe acute pancreatitis patients.

## Strengths and Limitations

### Strengths

This is a stepped-wedge cluster-randomized, multicenter, controlled trial providing high-level evidence about the impact of NS and a balanced crystalloid on plasma chloride concentration and renal function/AKI/renal failure, a significant consequence of severe AP.The data will be reviewed by an independent data safety monitoring board (DSMB) to ensure the participants' safety.

### Limitations

Mild acute pancreatitis patients who may also benefit from the use of balanced crystalloids will not be included;The study sample size is relatively small and not sufficiently powered to detect a difference in patient-centered outcomes like MAKE 30.

### Trial Status

The CLEVER-AP trial will be conducted between Apr 1^st^, 2021, to Mar 31^st^, 2022.

## Ethics Statement

The studies involving human participants were reviewed and approved by the Chinese Clinical Trials Registry (ChiCTR2100044432). Written informed consent for participation was not required for this study in accordance with the national legislation and the institutional requirements.

